### Sample size calculation

3.5

To the best of our knowledge, robust evidence on the effect size of robot-mediated interventions primarily aimed at usability and behavioral outcomes in individuals with neurocognitive disorders is currently lacking. Therefore, a formal sample size calculation based on statistical power is not feasible. The proposed sample size is determined according to a pragmatic approach, taking into account the epidemiology of apathy within the target population and previous studies in the field of robotic interventions and dementia, which typically include small sample sizes (often fewer than 20 patients per arm; Hung et al., 2021; Mancioppi et al., 2019; Moyle et al., 2019).

In line with these considerations, the study aims to enroll approximately 25 patients per arm who will complete the trial. Accounting for an expected attrition rate of approximately 6%, the total sample to be randomized was set at 80 patients, allocated with a 1:1:1 ratio directly at enrollment (exact allocation per arm may vary slightly depending on block randomization, approximately 27, 27, and 26 patients per arm, given block randomization). The primary analysis will be conducted on an intention-to-treat basis, including all randomized participants; a per-protocol analysis restricted to patients who complete the trial will be reported as a secondary analysis.

## Discussion

4

As the global population ages, the socio-economic burden of dementia in developed countries, such as Italy has reached significant dimensions (ISTAT, 2020), necessitating urgent responses (CENSIS, 2024). Within this context, apathy emerges as one of the most prevalent and distressing neuropsychiatric symptoms in mild cognitive impairment, mild behavioral impairment, and dementia (Mortby et al., 2022). To date, apathy has largely remained excluded from the focus of available pharmacological intervention studies (NICE, 2018; O'Connor et al., 2019; Oliveira et al., 2021). The RAPHAel protocol is designed to address this gap by testing whether robotic interventions can deliver structured stimulation and social engagement directly in the home setting. Namely, our protocol aims to migrate specialized rehabilitation from institutional settings directly into the patients’ homes, potentially extending personalized care to a broader population.

Despite the growing interest in socially assistive robotics for individuals with cognitive impairment, robust evidence supporting the clinical effectiveness of home-based robotic interventions specifically targeting apathy remains limited. Previous studies have generally involved small samples, focused primarily on feasibility or usability, or evaluated assistive rather than rehabilitative robotic systems (Hung et al., 2021; Mancioppi et al., 2019; Moyle et al., 2019). Moreover, few randomized controlled trials have directly compared different robotic approaches with an active standard-of-care intervention. The RAPHAel trial has been specifically designed to address these gaps by evaluating two complementary robot-assisted rehabilitation strategies against occupational therapy within a randomized controlled framework, while simultaneously integrating clinical, behavioral, and technology-derived outcome measures.

A fundamental innovation of the RAPHAel project is its shift from purely “assistive” robotics toward a “rehabilitative” model. By leveraging the principles of neural plasticity and cognitive reserve (Stern, 2006; Valenzuela and Sachdev, 2006; Esiri and Chance, 2012), we hypothesize that targeted non-pharmacological interventions can stimulate capabilities even in the presence of neurodegeneration.

The RAPHAel project employs a three-arm randomized controlled design to evaluate two distinct home-based technological interventions as compared to the current gold standard of occupational therapy. The first experimental approach features a tele-operated system (RoboXcare) dedicated to structured cognitive stimulation. This intervention, remotely facilitated by a neuropsychologist, targets specific domains, such as attention, memory, and executive functions, through a validated protocol characterized by systematically increasing difficulty levels. On the other hand, the second arm utilizes Pepper, an autonomous humanoid robot designed for conversational engagement; by connecting to a dedicated CAIR server, the system facilitates personalized dialogues tailored to each patient’s interests and life history, providing a platform for spontaneous social interaction without restrictions on frequency or duration.

Furthermore, the implementation of these interventions in the ecological context of the patient’s home offers unique advantages. Not only does it make the treatment more realistic and generalizable to daily life, but it also provides crucial support to caregivers, who often face high levels of stress and reduced quality of life. Consistently with recent trends in digital therapeutics (Matamala-Gomez, et al., 2020; Moccia, et al., 2021), RAPHAel also aims to pioneer the development of “digital markers”. By collecting in-depth metrics, such as social grasping kinematics and conversational metrics, we expect to establish objective measures for monitoring behavioral symptoms and the efficacy of future treatments.

### Anticipated results

4.1

The RAPAHel study has two primary expected outcomes. The first is to generate data useful for the development of digital biomarkers of behavioral disturbances in individuals with cognitive decline, with the purpose to facilitate the monitoring of the effectiveness of both pharmacological and non-pharmacological interventions. The second is to demonstrate the feasibility of robot-mediated interventions in the home setting for individuals with cognitive decline and related behavioral disturbances, yielding both direct benefits (for individuals with cognitive impairment or dementia) and indirect benefits (for caregivers/family members).

We anticipate that participants receiving the robot-assisted interventions will show improvements in apathy and social engagement relative to the baseline and that such improvement is comparable to the active occupational therapy control group, while also demonstrating good usability and acceptance of the proposed technologies, one of which (Pepper) has never been used at the patient’s home. We further expect that interaction metrics collected by the robotic platforms and kinematic parameters derived from the social grasping task will provide objective digital markers associated with behavioral changes and treatment response. These measures may contribute to the development of more personalized rehabilitation strategies for individuals with cognitive impairment.

Beyond the expected clinical benefits, the study is designed to evaluate the feasibility of implementing home-based robotic rehabilitation in real-world settings. Positive findings would support the integration of robotic technologies into routine clinical practice and provide evidence for scalable, home-based interventions that may reduce caregiver burden while increasing access to personalized rehabilitation.

While we acknowledge potential limitations, such as the pragmatic sample size common in robotic trials, we expect that the findings of this randomized controlled trial will clarify whether home-based robotic interventions are usable, safe, and potentially effective in reducing apathy-related behavior. In summary, the RAPHAel project will provide evidence on the feasibility, acceptability, and potential clinical value of home-based robotic interventions for apathy in individuals with cognitive decline, shaping the development of sustainable models for the healthcare systems of the future.

Ultimately, the RAPHAel trial is expected to provide an important step toward establishing evidence-based home-based robotic rehabilitation for apathy in cognitive impairment, while informing future multicenter trials and supporting the integration of personalized robotic technologies into routine dementia care.

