Behavioral and psychological symptoms of dementia (BPSD; Finkel et al., 1996) associated with neurodegenerative diseases may emerge at very early stages and can represent a distinguishing feature of certain atypical dementias, such as frontotemporal dementia or the dysexecutive/frontal variant of Alzheimer’s disease. Apathy, anhedonia, and lack of interest are among the most frequent BPSD and are often perceived as particularly burdensome in the relationship between the individual and the caregiver (Mortby et al., 2022). However, to date, no specific pharmacological intervention has proven effective in the management of apathy (NICE, 2018). Some evidence in the literature supports the effectiveness of non-pharmacological interventions for the treatment of non-cognitive symptoms in individuals with dementia or MCI; however, only a limited number of studies have specifically used improvement in apathy as an outcome measure (NICE, 2018; Koh et al., 1994; Oliveira et al., 2021; O'Connor et al., 2019). Some studies highlighted the role of occupational therapy (OT) in improving BPSD through personalized, home-based activity programs designed to engage individuals with dementia according to their abilities and living context. These interventions often involve caregiver participation and environmental adaptation within each patient’s home. Most OT interventions demonstrated benefits in enhancing social participation, overall wellbeing, and certain BPSD, such as depression and agitation (Graff et al., 2008; Gitlin et al., 2010), although they generally do not show a specific effect on apathy, with few exceptions (Nishida et al., 2017).

Furthermore, few studies examined the effects of robotic interventions on apathy in individuals with dementia or MCI. Existing studies primarily focused on assistive rather than rehabilitative purposes, and yielded limited evidence of effectiveness in improving apathy (Valentí Soler et al., 2015; Mancioppi et al., 2019; Yu et al., 2022).

Therefore, this paper presents the study protocol for the RAPHAel project, which aims to evaluate the efficacy of non-pharmacological interventions targeting apathy in individuals with dementia, MCI, or MBI. The study compares two robot-assisted intervention strategies, a tele-operated cognitive stimulation program and an autonomous conversational robot, against an active occupational therapy control condition, which is currently considered the gold standard.

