### Primary outcome measures

3.1

The primary objective of this study is assessing the clinical and behavioral effects of home-based robot interventions compared to standard occupational therapy.

The primary endpoints of the study are defined as follows:Clinical improvement of apathy in patients, assessed using:Apathy Evaluation Scale (AES)Yoni-48 TaskEdinburgh Social Cognition Test (ESCoT)International Affective Picture System (IAPS)Interaction metrics with robotic systems, including:Response times of system componentsNumber and type of conversation topics addressed, and number of characters in each sentence, spoken per topic (e.g., sports, cinema, cooking, travel)Tone of verbal responses (neutral, humorous, aggressive, etc.)Attitude toward discussion topics (positive, negative, neutral)Objects recognized in the environment, along with labels that classify the identified items and their spatial relationships—for example, a lamp or a vase placed on a table.Number of verbal interactions per minute with the robotNumber of physical interactions per minute (e.g., hand, head, tablet, or base contact with the robot).

These interaction metrics, namely, the frequency and spontaneity of verbal and physical engagement with the Pepper robot, will also be interpreted as clinical indicators of the patient’s willingness to engage, given that reduced initiation and engagement are core features of apathy.3.Sensor-derived and kinematic measures during social grasping tasks, collected via BMR4RAPHAEL wearable sensors and cameras:Integral of the acceleration vector (m/s^2^)Peak velocity amplitude (m/s) and timingExecution time, reaction time, and deceleration (absolute and relative)Maximum hand excursion (degrees) and timingAsymmetry and kurtosis of movement.

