### Statistical analysis

3.4

Initial data inspection will include descriptive statistics to summarize demographic and clinical characteristics and to identify potential outliers. Outliers will be evaluated according to standard practices, including visual inspection of boxplots and standardized residuals (values exceeding ±3 standard deviations), and decisions on their treatment (e.g., retention, transformation, or exclusion) will be justified and documented.

The distribution of each variable will be assessed using both visual (histograms, Q-Q plots) and statistical methods (Shapiro-Wilk test) to guide the choice of parametric or non-parametric analyses. For the main analyses, a two-way repeated-measures ANOVA will be conducted with Group (three levels: two robot-assisted interventions and one active control) and Time (three levels: T0, T1, T2) as factors. Post-hoc comparisons will be performed with appropriate correction for multiple testing.

Additionally, correlation analyses and regression models (both linear and logistic, where appropriate) will be conducted to explore associations between clinical outcomes, caregiver measures, and device-derived metrics, as well as potential predictive factors. All analyses will be conducted using (version 4.1.2; R Core Team, 2021) and Matlab (The Math Works, Inc., 2025) and/or equivalent statistical software, and significance thresholds will be set *a priori*.

Results will be reported as aggregated data to ensure participant anonymity.

Clinical data will be analyzed at the Department of Biomedical, Metabolic, and Neuroscience of the University of Modena and Reggio Emilia.

Device- and sensor-derived data, including kinematic and interaction metrics from robot-assisted interventions, will be analyzed in relation to clinical and behavioral outcomes by experts at the University of Genoa and the University of Florence.

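### The article anticipates robot-arm improvement comparable to occupational therapy, but its main analysis tests only for differences, so a non-significant result could not support that conclusion

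*Protocol article*

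**What the plan says.** **Anticipated result.** Section 4.1 (Anticipated results) expects that patients in the robot arms "will show improvements in apathy and social engagement relative to the baseline" and that "such improvement is comparable to the active occupational therapy control group".

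**Objective.** Section 3.1 (Primary outcome measures) gives the primary objective as "assessing the clinical and behavioral effects of home-based robot interventions compared to standard occupational therapy". It is not framed as superiority, non-inferiority or equivalence.

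**Analysis.** Section 3.4 (Statistical analysis): "For the main analyses, a two-way repeated-measures ANOVA will be conducted with Group" at three levels and Time at three levels (T0, T1, T2). "Post-hoc comparisons will be performed with appropriate correction for multiple testing". The remaining analyses are exploratory correlations and regressions. No numeric alpha is given.

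**Sample size.** Section 3.5 says that "a formal sample size calculation based on statistical power is not feasible" and sets about 25 completers per arm, about 6% attrition and 80 randomized.

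**Comparator.** The Introduction credits occupational therapy with benefits on participation, wellbeing and some behavioural symptoms, "although they generally do not show a specific effect on apathy, with few exceptions". It also calls the occupational therapy control the current gold standard.

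**The concern.** The only between-arm result on apathy that the article anticipates is similarity, and the only between-arm analysis it names looks for difference. The null hypothesis of that analysis is equality. Failure to reject it can mean that the arms are alike or that the trial is too small to tell, and a p-value above the threshold does not separate the two. If non-significance were read as comparability, a less precise trial would reach that reading more often, including when a robot is worse.

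The other half of the anticipated result, improvement from baseline, does not fill the gap. No arm is untreated, and patients enter because their NPI apathy score exceeds 2. Change within an arm therefore mixes any treatment effect with regression to the mean, attention and time. Nor does similarity to occupational therapy supply the missing evidence of benefit, because the article itself doubts that this comparator acts specifically on apathy.

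This matters because section 4.1 goes on to say that positive findings would support routine use of the robots.

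**Working it through.** **1. The plan's own figure.** 25 × 3 = 75 completers; 75 / (1 − 0.06) = 79.8, rounded up to 80. The stated total reproduces. There is no power statement to reproduce.

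**2. Inputs.**
- From section 3.5: n = 25 completers per arm.
- Assumed, because the article gives no value: two-sided alpha 0.05; outcome in SD units (SD = 1); correlation r of 0.5 to 0.7 between baseline and T1 for the adjusted figures.

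**3. Precision of one robot-minus-control difference.** Half-width of the 95% CI = t × s × √(2/n), with √(2/25) = 0.2828.
- Unadjusted, s = 1, 48 df: 2.011 × 0.2828 = 0.569 SD.
- Baseline-adjusted, s = √(1 − r²), 47 df:
  - r = 0.5: s = 0.866; 2.012 × 0.866 × 0.2828 = 0.493 SD.
  - r = 0.7: s = 0.714; 2.012 × 0.714 × 0.2828 = 0.406 SD.

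The Group by Time contrast from T0 to T1 amounts to comparing change scores, for which s = √(2(1 − r)). That gives 0.57 SD at r = 0.5 and 0.44 SD at r = 0.7, inside the same overall range.

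**4. How often a truly worse robot gives a non-significant result.** True deficit 0.5 SD, 25 per arm, noncentral t:

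| Analysis | Alpha 0.05 | Alpha 0.025 (two comparisons) |
|---|---|---|
| Unadjusted | 59% | 70% |
| Adjusted, r = 0.5 | 48% | 60% |
| Adjusted, r = 0.7 | 32% | 43% |

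The last column takes Bonferroni over the two robot-versus-control comparisons as an example, because section 3.4 does not name its correction.

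**5. Dependence on trial size.** For the same 0.5 SD deficit, unadjusted at 0.05, non-significance occurs in 78% of trials with 12 per arm, 59% with 25, 30% with 50 and 6% with 100. The rate falls only because precision improves; the robot is equally worse in every case.

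**6. What a formal non-inferiority claim would need.** One-sided 0.025, true difference 0, unadjusted, normal approximation. With 25 per arm and a margin of 0.5 SD, power = Φ(0.5/0.2828 − 1.96) = Φ(−0.19) = 42%. For 80% power at that margin, n = 2 × (1.96 + 0.84)² / 0.5² = 62.7, so 63 per arm: 189 completers, or about 202 randomized at 6% attrition. The smallest margin with 80% power at 25 per arm is (1.96 + 0.84) × 0.2828 = 0.79 SD, or about 0.69 to 0.57 SD with baseline adjustment at r = 0.5 to 0.7. The article gives no margin, so these are illustrations.

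**The case against.** The strongest reply is that the sentence is a forecast. It opens as an expectation, stands in the Discussion, and is neither a hypothesis nor an analysis rule. Section 4.1 names digital-marker data and feasibility as its two primary expected outcomes. The stated objective, comparison with occupational therapy, is one that a Group by Time analysis does address. Sections 4.1 and 5 also admit the limited sample, speak of preliminary evidence and potential effectiveness, and concede that attention effects cannot be fully separated from specific ones.

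Much of this stands, and it rules out several stronger readings that a reader might infer:

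- **That the plan adopts a rule of non-significance means comparable.** No section says so. The risk is that nothing in the text prevents that reading.
- **That the lack of a margin is itself the error.** A margin or a confidence-interval rule could sit in a full protocol or analysis plan that is not shown. The point is that the named analysis does not match the named expectation.
- **That occupational therapy has no effect on apathy.** The Introduction says only that a specific effect is generally not shown, and allows a few exceptions.
- **That section 3.5 says nothing can be computed.** It rules out only a power-based sample size, for want of effect-size evidence. Precision in SD units needs no effect size.
- **That 59% is the trial's error rate.** It is the unadjusted value at an assumed alpha, and baseline adjustment lowers it.

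The size of any regression to the mean is also unknown: selection is on the NPI apathy item, and carry-over to the AES depends on a correlation that the article does not give.

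What the reply leaves open is the inference itself. Caveats about sample size and preliminary evidence do not say that a non-significant difference will not be taken as comparability.

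**Conclusion.** The concern holds in this limited form: the difference-testing analysis in section 3.4 cannot, through a non-significant result, support the comparability anticipated in section 4.1. At about 25 completers per arm, the 95% CI would extend roughly 0.4 to 0.6 SD either side of the estimate, and a deficit of 0.5 SD would go undetected in about a third to three fifths of trials at 0.05. These figures rest on an assumed alpha, SD units and assumed baseline correlations. The conclusion does not depend on the exact values, since precision is limited across the whole range.

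Separately, neither improvement from baseline nor similarity to this comparator would by itself show that a robot reduces apathy. Even a successful non-inferiority result would leave that open unless the comparator's effect on apathy were established.

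**What to change.** - **Section 3.4:** base the between-arm conclusion on the baseline-adjusted robot-minus-control difference in AES at T1, for each robot, with its 95% CI. State that a non-significant difference will not be read as comparability and that change within an arm is descriptive.
- **Section 4.1:** remove the word comparable, or replace it with estimation of the difference from occupational therapy.
- **Section 3.5:** give the expected precision as a range with its assumptions: about ±0.57 SD unadjusted, and ±0.41 to ±0.49 SD adjusted at correlations of 0.7 to 0.5, with 25 completers per arm and two-sided 0.05.
- **Non-inferiority or equivalence:** make no such claim unless a justified margin is fixed in advance, and say that power would be low at this sample size.

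The first three changes need no extra patients or assessments. They do require AES at T1 to be singled out from the several primary endpoints for this conclusion, and they leave a less favourable anticipated claim. A non-inferiority design would cost more: at a 0.5 SD margin, about 202 randomized instead of 80 on the unadjusted calculation. The changes should be made before results are known, because a rule for reading the difference has little credibility if set afterwards.

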## Limitations

5

This study presents some intrinsic limitations, due to the implementation of innovative home-based robotic interventions. A first limitation concerns the unequal and non-standardized contact time across study arms. The occupational therapy control group follows the frequency defined by national care standards (Ministero della Salute, DPCM, 2017), the telerobot arm follows a fixed schedule of three 45-min sessions per week, while the Pepper robot arm allows for flexible, self-paced interactions with no upper limit. This design choice reflects the practical and technical characteristics of each modality rather than an attempt to equalize contact time, and it does not allow a complete separation between intervention-specific effects and non-specific effects related to attention and social contact, particularly in the comparison between the robotic arms and the active control group. Actual contact time in each arm will be recorded and may be used as a covariate in sensitivity analyses.

Furthermore, potential limitations include participant drop-out, variability in digital literacy among patients and caregivers, technical issues related to internet connectivity or device functioning, and differences in disease severity that could influence adherence to the intervention. To minimize these issues, all participants and caregivers will receive standardized training before the intervention, technical support will be available throughout the study, and the occupational therapist responsible for device installation will verify the correct functioning of the equipment. In addition, the pragmatic design of the trial and the relatively limited sample size should be considered when interpreting the findings. Nevertheless, the randomized controlled design and the inclusion of an active control group are expected to provide robust preliminary evidence regarding the feasibility, acceptability, and potential clinical effectiveness of robot-assisted interventions for apathy.

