
For robot-mediated interventions, an occupational therapist will install the device at the patient’s home and provide a 4G connection if needed. Patients and study partners will be instructed on device operation.

It could be argued that across the three intervention arms the substantial difference in contact time represents a limitation of the study protocol. However, this difference is an intrinsic consequence of the distinct nature of each intervention: the control arm adheres to the frequency defined by national care indications and therefore represents the best possible standard of care (Ministero della Salute, DPCM, 2017), the tele-operated robot follows a fixed schedule of three 45-min sessions/week, consistent with previous protocols (Realdon et al., 2016; Rossetto et al., 2023), and the Pepper robot, being autonomously available at the patient’s home, allows potentially unrestricted, self-paced interaction. Nonetheless, all these interventions pursue the same clinical objective—the reduction of apathy in patients with dementia. Hence, this heterogeneity in contact time is acknowledged as a limitation, thus it will be taken into account in the statistical analyses and in the interpretation of the results.

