### Randomization and blinding

2.4

Eligible patients will be randomized using the “blockrand” package in (version 4.1.2; R Core Team, 2021). Randomization will be performed separately for each recruitment center and, within each center, will be stratified according to clinical and demographics variables, including diagnosis, sex, age, years of education, MOntreal Cognitive Assessment (MOCA) score, and apathy severity as measured by the Neuropsychiatric Inventory (NPI) apathy subscale. The allocation sequence will be prepared by a researcher not involved in either treatment delivery or outcome assessments. Investigators responsible for treatment administration and evaluations will not have access to the randomization list. Once generated, the list will be uploaded to REDCap in a non-visible format. Upon the creation of each new patient record and study ID, REDCap will automatically assign patients to their study group according to the predefined allocation sequence. In addition, different user access levels within REDCap will ensure that group allocation remains concealed from outcome assessors.

Patients will be randomly assigned to one of the two experimental groups or to the active control group (1:1:1 ratio).

Given the nature of the interventions, blinding will not be feasible for recruiting clinicians, researchers administering the interventions, or patients. However, outcome assessments at baseline (T0), post-intervention (T1), and follow-up (T2), including clinical endpoints and clinical/psychological questionnaires, will be conducted by trained evaluators who are blinded to group allocation. In addition, data analysts will remain blinded to treatment assignment throughout the analysis phase.

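### The main model leaves out baseline adjustment, centre and the stratification factors, and the one covariate named, contact time, cannot safely adjust an arm contrast even in a sensitivity analysis

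*Protocol article*

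**What the plan says.** **Main model (3.4 Statistical analysis).** The plan states that "a two-way repeated-measures ANOVA will be conducted with Group (three levels: two robot-assisted interventions and one active control) and Time" is the main analysis, Time having the levels T0, T1 and T2. No covariate is given. The regression models mentioned afterwards explore associations and predictors; they are not the arm comparison.

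**Randomisation (2.4 Randomization and blinding).** "Randomization will be performed separately for each recruitment center and, within each center, will be stratified according to clinical and demographics variables". Besides centre, the section lists six patient factors: NPI apathy, MoCA, schooling, age, sex and diagnosis.

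**Contact time.** Two sections differ in strength. Section 2.2.2 (Rehabilitation interventions) says "this heterogeneity in contact time is acknowledged as a limitation, thus it will be taken into account in the statistical analyses", without a method. Section 5 (Limitations) says "Actual contact time in each arm will be recorded and may be used as a covariate in sensitivity analyses". Section 2.2.2 also presents the differing contact time as inherent in the three interventions. Section 3.1 (Primary outcome measures) reads how often and how spontaneously patients engage with Pepper as a clinical sign of willingness to engage, because low initiation is central to apathy.

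**The concern.** Two separate matters meet here.

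1. **Efficiency and calibration.** The design collects T0 values and stratifies on variables expected to be prognostic, but the stated model uses T0 only as an outcome and does not use the stratifiers. With about 25 completers per arm and no power calculation (3.5), precision that costs nothing should not be given up.

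2. **The wrong kind of covariate.** The only adjustment variable named is a consequence of allocation. Holding contact time fixed can remove a part of the treatment effect that runs through contact. It can also create a difference where none exists, if motivation or severity drives both contact and outcome. A contact-adjusted contrast could then be read as a cleaner estimate of the treatment effect, which it is not.

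**Working it through.** **The plan's own figure.** 25 completers × 3 arms = 75; 75 / (1 − 0.06) = 79.8, rounded up to 80. The stated total reproduces. It does not rest on power, so nothing below changes it.

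**Step 1: baseline as outcome level or as covariate.** Take one follow-up visit, equal variances scaled to 1, and correlation ρ between T0 and that visit. The document gives no ρ, so a range is assumed.
- Change from baseline: variance 2(1 − ρ).
- Baseline-adjusted: variance 1 − ρ².
- Ratio, adjusted to change: (1 + ρ)/2.

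Power is for a pairwise comparison at 25 per arm, two-sided 5% and an assumed difference of 0.5 SD (normal approximation).

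| Assumed ρ | (1+ρ)/2 | Change analysis equals adjusted analysis with this many times the patients | Power, change | Power, adjusted |
|---|---|---|---|---|
| 0.3 | 0.65 | 1.54 | 0.32 | 0.46 |
| 0.5 | 0.75 | 1.33 | 0.42 | 0.53 |
| 0.7 | 0.85 | 1.18 | 0.63 | 0.70 |
| 0.8 | 0.90 | 1.11 | 0.80 | 0.84 |

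The third column is the factor by which the change analysis needs more patients for equal precision. The gain is largest when ρ is low and shrinks as ρ rises.

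**Step 2: omitted stratifiers.** If the factors are perfectly balanced and explain a share R² of the variance of the analysed quantity, a nominal 5% test that ignores them has true size 2[1 − Φ(1.96/√(1 − R²))].
- R² = 0.1: 0.039
- R² = 0.2: 0.028
- R² = 0.3: 0.019
- R² = 0.4: 0.011

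The R² values are assumed. Perfect balance is the extreme case. With only two levels per factor, 2 centres × 2⁶ = 128 cells for 80 patients, so realised balance, and with it the conservatism, may well be weaker. The same count shows that the full cross-classification cannot be fitted.

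**Step 3: contact time.** Tele-operated arm: 3 × 45 min × 6 weeks = 810 min = 13.5 h as scheduled. Control: 8 home and 2 telephone sessions, length not stated. Pepper: no upper limit and no expected mean. All hours other than 13.5, all SDs and all correlations below are assumptions.

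*Simulation A:* no true effect; 3,000 trials of 80 patients; outcome scored so that higher means more apathy; control 8 ± 1 h, tele-operated 13.5 ± 1 h, Pepper 15 ± 6 h; contact correlated with apathy within the Pepper arm only. Without adjustment, differences are about 0 and rejection about 5%. With contact time as covariate:

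| Correlation in Pepper arm | Pepper − control, SD | Rejection | Tele − control, SD | Rejection |
|---|---|---|---|---|
| −0.2 | +0.21 | 9% | +0.17 | 7% |
| −0.4 | +0.44 | 23% | +0.34 | 18% |
| −0.6 | +0.67 | 49% | +0.52 | 38% |

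Here both robots are made to look worse. If mean Pepper contact is instead 5 h (SD 2 h), the Pepper shift changes sign: −0.19, −0.40 and −0.58 SD.

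*Simulation B:* a shared cause such as motivation acts in all arms; 26 per arm; outcome scored so that higher is better; Pepper mean 15 h. With no true effect, the adjusted tele-operated and Pepper contrasts move to −0.47 and −0.59 SD when control contact is 7.5 h, and to −0.27 and −0.38 SD when it is 10 h. Rejection is 16% to 36%. If instead the whole effect runs through contact, true differences of 0.36 and 0.45 SD (control 7.5 h) are adjusted to about 0.

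*No relation between contact and outcome:* there is no bias. In A the SE still rises from 0.271 to 0.327 (tele-operated, 21%) and from 0.274 to 0.361 (Pepper, 32%).

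**The case against.** **Omission is not bias.** Randomisation makes the change comparison valid, and T0 is in the model. This stands: the loss is of precision and calibration, and at ρ = 0.8 it is modest. A reader might infer that leaving out the stratifiers invalidates the main test; if anything it makes the test conservative.

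**Covariates may be in an analysis plan not shown.** That is possible, and silence would be no finding. But section 3.4 is not silent: it names the factors of the main model.

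**Contact time is not in the main model.** This also stands. A reader might infer from the firmer sentence in 2.2.2 that contact time biases the main arm comparison, or that it could overturn or rescue the main result. The document does not support that. The only place that names a method, section 5, makes it optional and confines it to sensitivity analyses, and section 3.5 sets the primary analysis as intention-to-treat in all randomised patients.

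**The sensitivity analysis has a purpose.** Section 5 admits that specific effects cannot be fully separated from those of attention and social contact, and removing the contact-mediated part may be the aim. That is a fair question, but a covariate in the arm comparison answers it only if nothing else drives both contact and outcome. Section 5 itself says disease severity could influence adherence, and section 3.1 treats Pepper engagement as an expression of apathy.

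**The contact-time figures rest on assumptions.** They do. They show that bias is possible, not how large it will be.

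**Conclusion.** The point holds in two parts of different weight.

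- **Main model:** valid but less efficient than it could be at no cost. Baseline adjustment reduces the variance to between 0.65 and 0.90 of the change-score variance for ρ from 0.3 to 0.8, assuming equal variances and a single follow-up visit. Omitting stratifiers can bring the true size down to between 0.039 and 0.011 for R² of 10% to 40%, under perfect balance.
- **Contact time:** a contact-adjusted arm contrast can be biased in either direction, and its size cannot be known in advance from the document. The bias is conditional on contact mediating the effect or sharing causes with outcome, and it is confined to the optional sensitivity analysis.

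The main model should be changed. The contact-time problem is one of labelling, interpretation and consistency between two sections.

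**What to change.** 1. In 3.4, analyse T1 and T2 as the outcomes, with T0 of the same measure, centre and the main stratification variables as main-effect covariates. Keep age, education, MoCA and NPI apathy continuous where possible. Do not fit the full cross-classification. Name the terms before unblinding, and keep the list short enough for about 75 completers.
2. Report contact time by arm. Do not present a contact-time-adjusted contrast as an adjusted treatment effect. Label any dose-response or mediation analysis as exploratory and non-randomised, and state its assumptions.
3. Bring 2.2.2 and section 5 into line, so that both say the same about whether and how contact time is used.

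The cost is a few degrees of freedom, a decision on which stratifiers to carry, and some rewording. The covariates are already recorded by T0, and the sample size is unchanged.
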